### Recruitment

A series of project information, sensitization, and recruitment meetings will be held with relevant township administrators; school principals, teachers, and other school staff; and parents and students. Schools, teachers, students, and parents will be enrolled at these meetings. Participants will be informed that participating in the project is voluntary. Consent and assent procedures will be carried out during these meetings and letters of agreement between schools and the project signed. Additional meetings to inform healthcare workers in hospitals and health centers and training on how to collect patient data following Good Clinical Practice (GCP) guidelines will also be carried out.

### Randomization and blinding

Allocation of interventions will be done after baseline collections (described below). Of the 46 eligible schools, 23 will be allocated to the intervention arm and 23 to the control arm. This will be accomplished by an open public lottery event. At this event, representatives from each school will attend, including regional and township health and educational representatives, teachers, parents, and students. Information about dengue and the goals of the project will be given. The reasons for randomization, its procedures, and the concepts of intervention and control will be explained. Attendees will also have a chance to ask questions about dengue, vector control, health seeking behaviors, personal experiences of dengue, and specific details about the project. The lottery will be carried out as follows. Small pieces of paper, indistinguishable from one another, numbered from 1 to 46, will be folded and placed in non-transparent envelopes and mixed in a bowl. Each number represents a cluster (school) and a list of the schools with their respective number will be consulted during the process. A large screen with the numbered list of school names will be shown above the bowl, visible to everyone. A person not involved in the study, and accepted by all participants, will be selected to make the draw. Two flip boards with large sheets of paper will be placed on either side of the bowl with the heading ‘Intervention’ and ‘Control’ (in Burmese). The first number drawn (representing a specific school) will be assigned to the Intervention arm, the next number/school drawn will be assigned to the Control arm, and so on. Following the draw, the implications of being in either of the two arms will be discussed and the roles of participants, health volunteers, and sub-district hospital staff will be reviewed. By following this lottery scheme, the interventions are allocated at the same time as the sequence is generated, obviating the need for allocation concealment. At this meeting we will take care not to provide any information about planned dengue control interventions that will be used in the trial to participants from the control arm to minimize contamination between the groups. 

The study is unblinded for both participants and data collectors due to the nature of the intervention, e.g., it is not feasible to use placebo interventions of larvivorous fish.

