### Study setting and participants

The study is planned to be conducted in South Dagon and Shwepyithar townships in Yangon Region, Myanmar (
Figure 1). These townships were selected out of the 45 in Yangon because of high dengue incidence and absence of other dengue projects. The population in South Dagon is ca. 307,000 and in Shwepyithar ca. 287,000. During 2013–2018 there were a total of 1,465 reported dengue cases (mean 244/year) and 15 deaths in South Dagon and 1,420 cases (237 cases/year) and eight deaths in Shwepyithar. These two townships represented approximately 12% of all reported dengue cases in Yangon Region during this period. There are 46 middle schools and high schools in these two townships, 20 in South Dagon and 26 in Shwepyithar. In 2019, there were an average of 250 sixth grade students per school. 40 high or middle schools will be included in the study (
Table 1). In each school approximately 40 sixth grade students (1–2 classes) will be selected based on feasibility, logistics, and willingness to participate. Each school and its catchment area (buffer zone) will be mapped. Non-overlapping school catchment areas that include students’ households represent the study clusters. Eligibility criteria are described in
Table 1. The delineation of school catchment area will consider mosquito flight distance from schools, but also providing sufficient buffer zones between adjacent catchment areas to avoid contamination between intervention and control schools. It is anticipated that a minority of students (<10%) will live in a different school catchment area within the two study townships. Due to the current health and security situation in Myanmar, the project has been terminated by the donor, but the protocol forms a basis for future implementation in Myanmar or elsewhere.

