^. Lack of data on adult mosquitoes in the study area precluded a sample size calculation for the quantitative secondary outcomes on adult mosquitoes. However, the number of adult mosquitoes in the area is expected to be large
^
47
^, thus giving substantial power to detect differences between the two arms. All 46 schools will be included in the study, using an equal cluster size of 23 schools per arm. Both arms (intervention and control) will be represented in each township. The power calculations were performed in Stata 16.

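### The school lottery is not stratified by township, so balance across the two townships is left to chance when two separate draws would secure it at almost no cost

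*Protocol article*

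**What the plan says.** The allocation procedure is in the protocol article under *Randomization and blinding*. The split is fixed at equal arms: "Of the 46 eligible schools, 23 will be allocated to the intervention arm and 23 to the control arm". Slips "numbered from 1 to 46, will be folded and placed in non-transparent envelopes and mixed in a bowl"; the first school drawn goes to intervention and "the next number/school drawn will be assigned to the Control arm, and so on". The procedure mentions no strata, no separate draws and no restriction on the order.

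Two other sections bear on it. *Sample size* states that "Both arms (intervention and control) will be represented in each township". *Study setting and participants* gives the township counts: "There are 46 middle schools and high schools in these two townships, 20 in South Dagon and 26 in Shwepyithar".

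The number of schools is not consistent. *Study setting and participants* says "40 high or middle schools will be included in the study", while *Sample size* says "All 46 schools will be included in the study, using an equal cluster size of 23 schools per arm" and the lottery also uses 46.

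Under *Data analyses*, the primary outcome is analysed by Poisson regression on cluster counts, or negative binomial if over-dispersed. No covariates are named there, and a detailed SAP is to follow before database lock.

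**The concern.** The plan treats township as something the allocation should respect, yet the draw takes no account of it. With two townships and one year of incidence data, a chance excess of one arm in one township matters if the two have different dengue years. The *Discussion* itself notes strong spatial and temporal variation in dengue transmission and the difficulty of depending on the particular year observed.

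At stake are how comparable the arms are in the one draw that is made, and how much between-township variation ends up in the error of the treatment comparison. Unlike the choice of model terms, this cannot be left to a later SAP: once the public draw is done, its township split is fixed.

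**Working it through.** **The plan's own figures.** Township cases for 2013–2018 are 1,465 and 1,420, which sum to the stated 2,885 (about 480 a year). On the plan's own basis (23 schools per arm, 40 person-years each, 0.26 against 0.18 per person-year, ICC 0.01), the design effect is 1 + 39 × 0.01 = 1.39. Power is then 85–87% for Poisson rates and 93–94% for two proportions, in line with the stated value above 80%. That calculation has no township component, so it neither supports nor undermines the point here.

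**1. Distribution of the township split.** Alternating arms along a random order is a simple random choice of 23 schools from 46. The number of South Dagon schools in the intervention arm is therefore hypergeometric (46 schools, 20 in South Dagon, 23 chosen), with mean 10 and SD 1.70.

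| South Dagon split, either direction | Probability |
|---|---|
| exactly 10/10 (so 13/13 in Shwepyithar) | 0.233 |
| 12/8 or worse | 0.373 |
| 13/7 or worse | 0.136 |
| 14/6 or worse | 0.036 |
| one arm absent from South Dagon | 6 × 10⁻¹⁰ |

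**2. Consequence at the documented average rates.** Incidence is 1,465/(6 × 307,000) = 79.5 per 100,000 per year in South Dagon and 1,420/(6 × 287,000) = 82.5 in Shwepyithar, a ratio of 0.96. Assume each township's population and cases are spread evenly over its schools: 15,350 people and 12.21 cases per school in South Dagon, 11,038 and 9.10 in Shwepyithar. With no intervention effect:

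- 12/8: (246.6/305,623) ÷ (234.2/288,377) = 0.994.
- 13/7: (249.7/309,935) ÷ (231.1/284,065) = 0.990.

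The shift is 1% or less.

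**3. Consequence if the townships diverge in the trial year.** The documents give no single-year township rates, so the township rate ratio *r* is an assumption, shown over a range, with equal catchment populations. If the intervention arm receives *k* schools of the higher-rate township (taken as South Dagon), the no-effect rate ratio is [k·r + (23 − k)] / [(20 − k)·r + (3 + k)].

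| r | 12/8 | 13/7 |
|---|---|---|
| 1.5 | 29/27 = 1.07 | 29.5/26.5 = 1.11 |
| 2 | 35/31 = 1.13 | 36/30 = 1.20 |
| 3 | 47/39 = 1.21 | 49/37 = 1.32 |

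If the control arm has the excess, the values are the reciprocals (for example 0.89 at 12/8 and 0.83 at 13/7 for r = 2). The planned effect is a ratio of about 0.70.

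**4. Precision.** This was simulated with 46 clusters averaging 10.5 cases, Poisson variation, equal populations, the single draw and no township term. With an over-dispersion correction (quasi-Poisson, standing in for the negative binomial), type I error stays near 5%. Power for a ratio of 0.70 falls from about 93% at r = 1 to 84% at r = 1.5 and 67% at r = 2. Stratifying the draw without a township term gives about 74% at r = 2, because the township variance is still in the error term. The gain therefore needs both the draw and the model term.

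**5. Split under separate draws.** 20/2 = 10 and 26/2 = 13, so 10/10 and 13/13 with certainty, and 23 schools per arm.

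**The case against.** A reader might infer that the lottery contradicts the *Sample size* section. It does not: that section promises only that both arms will be represented in each township, and the single bowl delivers this almost surely. It does not promise balance.

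A reader might also infer that the trial's estimate will be biased. Simple randomisation is valid, and over repeated draws the estimate is unbiased. About 63% of draws are 11/9 or better (1 − 0.373), and the documented average rates imply a negligible shift. The larger figures rest entirely on an assumed single-year divergence. The *Discussion* speaks of spatial and temporal variation but does not say that it follows township lines. Nor do the documents say that outbreaks or test reporting are organised by township: case detection runs through all hospitals and health centers in both, with project-supplied test kits.

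Finally, the article names no township term, but covariates are commonly settled in the SAP, so that silence is not an error. If a township term is fitted, most of the harm from a poor split goes. With equal variance per cluster (assumption), information relative to the balanced split is (12×8/20 + 11×15/26)/11.5 = 97% at 12/8 and (13×7/20 + 10×16/26)/11.5 = 93% at 13/7.

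All of this stands, and it limits the point to an improvement. It does not remove it: the draw is fixed by the protocol, cannot be repaired afterwards, and can be balanced for almost nothing.

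**Conclusion.** The point holds as an inexpensive design improvement, not as an error or a contradiction. The single draw leaves township balance to chance, with 12/8 or worse in South Dagon in 37% of draws and 13/7 or worse in 14%. On the 2013–2018 averages this hardly matters (about 1%). In a year when one township has 1.5 to 3 times the other's rate, the no-effect ratio would move to 1.07–1.21 at 12/8 and 1.11–1.32 at 13/7, or the reciprocals. Those values assume equal catchment populations and no township term in the model. The loss is in conditional balance and precision; validity over repeated draws is intact. The split probabilities assume that all 46 schools enter the draw. Although the project was terminated, the article offers the protocol for future use, so the change is still worth making.

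**What to change.** - At the same public event, hold two draws: one for the South Dagon schools and one for the Shwepyithar schools, alternating arms within each. With 20 and 26 schools this gives 10/10 and 13/13.
- Reconcile the 40 schools in *Study setting and participants* with the 46 in *Sample size* and *Randomization and blinding* before the draw. If a township ends up with an odd number of schools, balance there is to within one school, and the second draw should start with the arm that keeps the totals equal.
- Include township, as the stratification factor, as a fixed effect in the primary model; the SAP is a natural place to state it.

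The cost is a second bowl at an event already planned and one degree of freedom among 46 clusters.

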### Data collection

**
*Disease surveillance.*
** The primary outcome will be assessed by passive case detection in communities and in schools. The number of dengue cases in communities will be assessed during the study period (
Figure 2) through all hospitals and health centers in the two townships. These will be supported by monthly visits and provision of rapid diagnostic test (RDT) kits by the project. Cases of fever in participating schools will be monitored during school hours. In both communities and schools, fever cases with dengue-like illness fitting the WHO case definitions using clinical symptoms (fever, severe joint and muscle pain, intense headache, rash, etc.) will be recorded and RDTs performed using an antibody/antigen RDT (SD BIOLINE Dengue Duo NS1/IgG/IgM test kit, Standard Diagnostic Inc., Korea). Students and staff in schools will be referred to a nearby participating hospital, clinic, or school health medical offices for confirmation using RDTs as above. Written informed consent will be taken from each person who agrees to participate in the study. The RDT cassette will be used for confirmation of dengue virus and serotype using polymerase chain reaction (PCR).

**Figure 2. f2:**
[figure not shown]
Time schedule of enrolment, interventions, and pre- and post-allocation data collections based on Standard Protocol Items: Recommendations for Interventional Trials (SPIRIT) checklist
^
48
^. Arrows indicate continuous activities. Dashed arrow indicates that some of the vector control interventions will continue until June Year 2. Primary and secondary outcome measures in parentheses; see
Table 2 for further details.

The secondary disease outcomes will be assessed by seroprevalence assessments in schools and households at baseline (June Year 1) and at two follow-ups (four and eight months after baseline) and seroconversions between these two time points. In each school, a total of 40 students, teachers and staff (20 randomly selected 6
^th^ grade students, 20 randomly selected students in grade 1–5 based on feasibility and financial reasons) will be asked to provide a finger prick blood sample for a dengue RDT. Similarly, seroprevalence will be assessed in 40 households per school catchment area of which 20 will be students’ households and 20 randomly selected households in each school catchment area. One randomly selected person (any age >1 year old) in each household will be selected. Thus, there will be 20*23 = 460 individuals in each group (6 graders, grades 1–5, student households and other households) which permits detection of a 30% difference in seroconversion between the two study arms allowing for a 10% dropout rate, with 80% power and 5% significance. The presence of dengue antibodies (IgG and IgM) will be confirmed by a finger prick blood sample of 10μL and a rapid diagnosis test (RDT) kit (SD BIOLINE Dengue IgG/IgM, Standard Diagnostic Inc., Korea). A seroconversion will be determined when an RDT negative person becomes positive in a subsequent collection. Written informed consent will be taken. Data on potential confounders, e.g., age, sex, residence, travel history, and previous dengue history will be collected for each person using a short case report form (CRF).

**
*Mosquito collections.*
** Mosquitoes will be collected in each of the selected 46 schools and in at least five of the 20 selected households per school at baseline (June Year 1) and at three follow-ups (four, eight, and 12 months after baseline). In each school, adult mosquitoes will be collected using battery-driven aspirators for 15 minutes indoors (classrooms, canteen, toilets) and 15 minutes outdoors (at typical student gathering points, e.g., in vegetation). In each school, all breeding sites will be inspected and the following recorded: number of total containers, number of wet containers, number of containers positive for mosquito immatures (all genera and species), container type, and location (indoors/ outdoors). Mosquito larvae will be collected from all positive containers using regular sweep nets, dippers or strainers. Pupae will be collected using the pupal-demographic survey method
^
5
^ and the single water-surface sweep-net procedure for large containers
^
49
^. Mosquito collections in households will be done in the same way, except that adult mosquitoes will be aspirated for 10 minutes indoors (living room, bedroom, toilet, kitchen) and 10 minutes outdoors (e.g., in vegetation). In addition, entomological monitoring, one continuous week each month, will be done using BG-GAT ovitraps (glue strips) in both schools and households and. Traps will be managed by students as part of the enhanced school health curriculum and hands-on activities and will be compared with data collected by project teams. After the one week, mosquitoes on glue strips will be collected by project staff and identified. Species composition of mosquito larvae will be determined (
*Ae. aegypti, Ae. albopictus, Culex, Anopheles,* and ‘Others’).
*Aedes* pupae will be identified and sexed using published keys
^
50
^. Adult mosquitoes will be sorted by sex and identified to species level (
*Ae. aegypti, Ae. albopictus, Culex* spp. and ‘Others’) using a stereomicroscope. Presence of blood and blood digestion status (Sella’s stages) of female mosquitoes will be determined by external examination of abdomens. Dissection will be done in a sample of
*Ae. aegypti* and
*Ae albopictus* to assess their parity status. A commercially available DENV NS1 ELISA kit, the Platelia Dengue NS1 Ag kit (Bio-Rad Laboratories; Catalogue no. 72830), will be used to detect DENV in a sample of collected mosquitoes. Heads and thoraces of individual adult mosquitoes will be stored separately in 1.5 mL Eppendorf tubes. The abdomens will be pooled (five-10 mosquitoes per pool depending on catches) and stored in 1.5 mL Eppendorf tubes. Mosquitoes will be stored in -20°C. Virus detection will be performed on pooled and individual specimens using real-time RT-PCR (qPCR) and primers and probes targeting all four DENV serotypes
^
51
^. Positive samples will be submitted to a second run specific qPCR to determine the DENV serotype
^
52
^. 

**
*Knowledge, attitudes, and practices (KAP).*
** KAP measurements regarding dengue and vector control in students, parents, and teachers, will be assessed using pretested surveys on electronic forms on computer tablets. Endpoint sum KAP scores on a scale from 1–10, where 10 indicates the highest score, will be calculated for students and parents. KAP surveys will be done at baseline (June Year 1) and at three follow-ups (four, eight, and 12 months after baseline). Additional methods to assess changes in KAP and behaviors include key informant interviews, focus group discussions, in-depth interviews, and observations. Data for the behavioral models (below) will be collected through validated constructs included in the KAP surveys.

**
*Behavioral assessment.*
** Despite the widespread application of KAP measurements, a common limitation is that these assume all behaviors to be rational and requiring a high level of cognitive effort. KAP measurements fail to take into account irrational determinants of human behavior such as heuristics (i.e., adaptive-thinking approaches when making decisions in complex situations) and cognitive biases (i.e., cognitive pitfall where people make systematic reasoning errors resulting from reliance on mental shortcuts) stemming from behavioral economics. Behavioral economics is a discipline combining both economics and psychology, which aims to provide an alternative perspective to the assumption that behavior is governed by rational decision making, as exemplified in traditional economics
^
53
^. The behavioral assessment will be conducted to include relevant factors (e.g., heuristics, biases) influencing dengue prevention, in addition to the factors captured by the KAP measurement. These factors will be identified through the literature and formative research. Results from the behavioral assessment will be used to develop a more comprehensive model to understand and predict people’s behavior in relation to dengue control and prevention. Results and models will be compared between intervention and control arms and between pre- and post- intervention groups. This will allow estimation of direct and indirect effects of the interventions on vector control behaviors. Data for the models will be based on validated constructs, representing the identified behavioral factors, included in the KAP surveys. Constructs are abstractions that are created and validated by researchers in order to conceptualize a latent variable, which is correlated with scores on a given measure, although not directly observable. The scores of each measure will be recorded on a six-point bipolar scale (e.g., good-bad), or on a six-point Likert scale in which the respondents will present their opinion on a scale ranging from strongly disagree to strongly agree and adjusted for children’s cognitive skills
^
54,
55
^. Structural equation modeling will be used to validate and measure the model parameters (see data analysis).

**
*Engagement assessment.*
** Degree of engagement among students, parents, and teachers in vector control activities will be assessed using a set of qualitative methods, including photovoice
^
56
^, in-depth interviews, and focus group discussions. In the photovoice sub-study students will take photographs that reflect their experiences and perspectives, engaging them in dialogue on community health issues and reaching influencers and key stakeholders to catalyze social and behavioral change. Thus, students will develop an understanding of perspectives and understanding of mosquitoes, vector control, and any behavioral changes in relation to vector control activities, including unanticipated changes or consequences as a result of participation in the intervention. A group of approximately 10 students in four intervention schools, two in each township, will be invited to participate. Students will be trained in how to use cameras and on ethical issues associated with taking photos, and subsequently asked to generate photo assignments related to dengue and the dengue control interventions. A facilitator will moderate group discussions with participants whereby ‘trigger’ photographs are selected through a structured activity using a Freirean-based inductive questioning technique
^
57
^ used to catalyze critical dialogue to encourage reflection and generate new understanding of the issue students choose to highlight in their photographs. Teachers’ engagement will be assessed through in-depth interviews (approximately 23 teachers both pre- and post-intervention to include all intervention schools). Additionally, there will be two focus group discussions conducted post-intervention. With teachers, the following topics will be discussed: 1) roles and responsibilities in vector control education/activities; 2) school outreach activities; and 3) operational or social challenges of education and knowledge transfer to the wider community. Parental engagement will be assessed using in-depth interviews held during parent-teacher meetings (approximately 46 parents, two parents per intervention school). This will gauge the effect of the intervention on bi-directional knowledge flow and engagement between schools, households and the wider community. In particular, interview guides for parents will explore five areas relating to community engagement and the social context of the education and knowledge transfer interventions: 1) personal history (migration, poverty, conflict); 2) perceived health problems (dengue/fever concepts); 3) perceptions of vector control activities; 4) involvement in the school outreach interventions; and 5) perspectives and experiences related to community engagement for vector control and prevention throughout the whole intervention
^
58
^.

**
*Process evaluation.*
** A systematic process evaluation in the intervention arm will be conducted to assess implementation fidelity and adaptation, as well as perception of the dengue control interventions. Implementation fidelity, i.e., the extent to which the intervention was implemented as intended will be assessed, as will adaptation, i.e., the extent to which participants introduce changes to the original components/activities of the intervention to address contextual needs and challenges
^
59
^. The conceptual framework for implementation fidelity developed by Carroll
*et al.*
^
60
^ will be applied using specific process evaluation measures (
Table 3). Implementation fidelity will be assessed using an index score (ranging from 1 to 10) comprising variables that assess intervention exposure, dose, adherence, quality of delivery, program adaptation, and responsiveness. Index score cards will be developed for both the vector control and education/knowledge transfer interventions. The vector control interventions will be assessed through observation in school premises and households during four visits after implementation of the interventions (
Figure 2). The first three visits will be performed during the trial year, a follow-up visit will measure sustainability of the vector control activities. The index score cards for measuring vector control fidelity will include measurements of lid coverage, guppy fish and trap maintenance and waste management.

**Table 3. T3:** Process evaluation measures.

Measure	Description	Unit	Frequency of data collection	Details
Implementation fidelity of the vector control interventions	The extent to which the vector control activities were implemented as intended at schools and in households	Sum scores on a scale from 1–10, where ten indicates the highest score	4 times: - Jul. Year 1, - Nov. Year 1, - Mar. Year 2, - Jun. Year 2.	Assessed by observation and using index scorecards
Implementation fidelity of the education/knowledge transfer interventions	The extent to which the education/ knowledge transfer activities were implemented as intended by teachers	Sum scores on a scale from 1–10, where ten indicates the highest score, logbooks and qualitative data	4 times: - Jul. Year 1, - Nov. Year 1, - Mar. Year 2, - Jun. Year 2.	Assessed by observation and using index scorecards, as well as through logbook data collection
Reflection and adaptation of the intervention components	To develop an understanding of perceptions and experiences related to the education/ knowledge transfer interventions	Logbooks, qualitative data and code book.	2 times: - Nov. Year 1, - Mar. Year 2,	Assessed using teachers’ logbooks and qualitative methods: in-depth interviews and focus group discussions

The education and knowledge transfer interventions will be measured through observation using video recordings as to minimize social desirability and observer bias. The recordings will take place at four key time points: first when MOE and MOHS representatives deliver the enhanced curriculum to the teachers; then two times in the school context, when teachers deliver the curriculum to the students; and finally, a follow-up measurement of sustainability and adaptation, when the representatives of the MOE and MOHS deliver the curriculum to a new group of teachers for the upcoming schoolyear. As described above, the curriculum, and associated teachers’ manuals, will be developed through a participatory approach which will result in the development of the core components of the education/knowledge transfer intervention. Accordingly, the instruments to measure implementation fidelity of these interventions will be developed based on these core components and included in the index score card. The score card scores will be compiled into a comprehensive implementation fidelity index, similar to what has been used in water, sanitation and hygiene interventions
^
61
^. Teachers will be trained in using a logbook for documenting their experiences with the curriculum and the manual, to be able to record their own implementation fidelity and adaptation from the educational/knowledge transfer interventions. The logbook assessment will focus on the dynamics of the educational interventions, the teachers’ roles, adaptation to changes brought about by activities, implementation fidelity moderating factors (i.e., comprehensiveness of policy description, strategies to facilitate implementation, quality of delivery, and participant responsiveness), barriers, and facilitators of the implementation, and any unintended effects
^
62
^. Notes from the logbooks will be compiled into a manual that will serve as adaptation guidelines for the following years.

In addition, focus group discussions and in-depth interviews with parents and students will be conducted to develop an understanding of perceptions and experiences related to the education/ knowledge transfer intervention. The total number of discussions will be guided by the principle of data saturation, but there will be at least five focus groups (during two time points) with parents and students, respectively; and 20 in-depth interviews to elicit more nuanced data on emerging themes stemming from the focus groups. Qualitative data will be transcribed in the language in which it was conducted, translated into English and back translated to ensure accuracy. Findings from the quantitative and qualitative data will be triangulated to provide a comprehensive overview of the implementation process.

**
*School and household surveys.*
** School infrastructure surveys will be conducted at baseline in all schools to determine number of students, teaching and non-teaching staffing capacity personnel, existing health activities, facilities (e.g., classrooms, water and sanitation and hygiene facilities). A household survey will be conducted in all households of the participating students. It comprises a household questionnaire with the number of people living in the house (household roster), and their age, sex, level of education, occupation, and whether each inhabitant is a permanent member of the household. In addition, data will be collected on room occupancy, household assets, socioeconomic status, type and quality of house structure (roof, walls, ceilings, and floors), sanitation facilities, household water management practices, source of drinking and non-drinking water, solid waste collection and disposal, hygiene practices domestic animals, and mosquito control activities. The household roster will be updated at each entomological data visit. The geographical coordinates of each school, participating student’s households and school catchment areas will be mapped using handheld Global Navigation Satellite System (GNSS) devices and satellite imagery combined in a Geographical Information Systems (GIS).

**
*Climate and environment.*
** Data on rainfall, temperature, and humidity will be collected by measurements in schools, as well as from nearby meteorological stations. Household densities (crowding) in school surroundings and school catchment areas will be collected from annotation of satellite images, as will land use including the presence of non-residential areas, vegetation, and water bodies.
*
**
**
*

